This paper presents the protocol of a population-based observational study to examine the work experiences in adults with colorectal cancer. We aim to describe changes in work participation at two points in time within a 12-month period, identify the key predictors influencing work participation and time to work re-entry, quantify the extent of physical and cognitive limitations at work and the role of work on HRQoL. The results of the study will provide valuable information for individuals facing cancer, health professionals, supportive care services and government about the reasons for work cessation, the mechanisms people use to remain working and existing workplace support structures.

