### Aims and hypotheses

The key aims of the study are to:

1. Describe *transitions *in employment participation following a primary diagnosis of colorectal cancer within a 12-month period compared to individuals without cancer;

2. Identify the key factors influencing *work participation *during or after cancer treatment compared to individuals without cancer;

3. Identify the key factors influencing *time to work re-entry *after cancer treatment among individuals taking work leave for their cancer treatment;

4. Investigate the influence of changes in employment participation over a 12-month period on *HRQoL *at time 2 among individuals with cancer compared to those without cancer; and

5. Quantify the extent of *physical and cognitive limitations *at work (work disability) in individuals following a primary diagnosis of colorectal cancer.

We hypothesise that:

1. The proportion of middle-aged working adults with a primary diagnosis of colorectal cancer who substantially alter their work hours (i.e. by ≥20%) or stop working by 12 months after diagnosis will be more than 15% higher than among middle-aged working adults in the general community;

2. The key barriers to work participation or timely work re-entry after cancer will include regional or metastatic cancer at diagnosis, age, fatigue at six months, adjuvant therapy, living with an employed partner, limited work autonomy and low income; and,

3. Study participants who substantially reduce their work hours or leave the work force against their choice, will have clinically lower HRQoL scores at 12 months compared to those who remain employed at 12 months.

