### Specific questionnaire items and measures

*Generic baseline socio-demographic information*for the cancer and comparison groups will include items on age, gender, education level, country of birth, culture, marital status, household income, health and other insurances, postcode of residence, number and age of children.

*Participants' work situations, generic HRQoL, health behaviours and conditions*will be collected at both time-points (Table 1) with identical items for the cancer and comparison groups. Work situation items include a compilation of validated tools from Australian government surveys (eg Australian Bureau of Statistics (ABS) Labour Force Survey, ABS 1999 Survey of Living Standards) and ask about: employment status, usual and preferred weekly hours, reasons for working part time, occupation, occupation change, industry, trade union membership, paid sick leave, paid holiday leave, expected resignation or dismissal, supervisory responsibilities, employer type, workplace size, job satisfaction, if the respondent has a disability, type of disability, disability commenced in the last year, impact of disability on work probability, financial strain (e.g., access to emergency funds, bills paid late), intended age of retirement and intentions of stopping work during next three years. Generic HRQoL will be evaluated using the widely-used and validated Medical Outcomes Survey Short Form (SF-36). Physical activity estimates will be obtained via the International Physical Activity Questionnaire (short-form) [19]. Other standard health behaviours and conditions (smoking, alcohol consumption, height, weight and chronic illnesses) will also be asked.

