### Analyses

All analyses will include gender as a factor and will test for interactions of gender with other factors in the model. Gender differences are important, as not only do men and women have different work participation rates, work hours and occupation types in the general population [17], they respond and adjust differently to illnesses, have different health behaviours and other risk factors for cancer [24]. Where no effect modification is observed, pooled results will be presented. Socio-demographic characteristics will be compared at baseline to identify any statistically significant differences between the cancer and comparison groups. Descriptive analyses will be conducted to chart employment transitions over the year since diagnosis among the cancer group and over 2009-2010 year period among the comparison group. Although the first time point for the cancer group is six months after diagnosis, participants are asked to recall work circumstances (occupation type, hours worked, industry etc) at the time of diagnosis (retrospectively) and at time 1 (six months after diagnosis). Separate multivariable logistic regression modelling will identify explanatory variables that are significantly associated with work participation in the cancer and comparison groups. For these models, adjusted odds ratios with 95% confidence intervals and p-values will be computed. Cox proportional hazards models will assess time to work resumption in the participants with cancer and significant correlates of timely work re-entry. Mixed-effects modelling for the cancer group will be used to examine change in HRQoL scores (time 1 - time 2) by participants who reduce or leave in that time versus those who do not. We will also compare HRQoL scores between the cancer and comparison groups at time 2. Data on work limitations measured in the cancer group will be scored across the four domains and mixed-effects modelling undertaken to assess changes in scores between time 1 and time 2. Reasons for study withdrawal in the cancer sample will be closely monitored. Descriptive analyses of baseline variables for the 'completers' and 'non-completers' will identify any possible bias and the source and, if necessary, subsequent analyses will be weighted accordingly. In the comparison group, only responders at both HILDA Waves 9 and 10 will be included.

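### Hypothesis 3 is limited to work change against the person's choice, but the only stated HRQoL analysis by work change pools chosen and unchosen change

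*Protocol article*

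**What the plan says.** Under Aims and hypotheses in the protocol article, the exposed group of hypothesis 3 is participants who "substantially reduce their work hours or leave the work force against their choice". The prediction is that they "will have clinically lower HRQoL scores at 12 months compared to those who remain employed at 12 months".

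Under Analyses, the HRQoL model by work change is a mixed-effects model in the cancer group. It examines change in score from time 1 to time 2 "by participants who reduce or leave in that time versus those who do not". Two other analyses involve HRQoL or health status:

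- In the same section: "We will also compare HRQoL scores between the cancer and comparison groups at time 2". This is a comparison of cancer with non-cancer participants.
- A two-stage simultaneous probit model, in which health status is treated as endogenous to work participation.

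Aim 4 asks how changes in employment participation influence HRQoL and sets no condition on choice.

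The work items under Specific questionnaire items and measures include "employment status, usual and preferred weekly hours, reasons for working part time". The same list covers whether the person expects to resign or be dismissed, the age at which they plan to retire, whether they plan to stop work within three years, and disability and its effect on work. These are collected at both time points.

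**The concern.** The choice condition sets hypothesis 3 apart from a general statement that people who work less feel worse. The planned grouping does not carry it. A person who retires as intended and a person forced out by illness fall into the same exposed group. Cases are aged 45-64, so chosen retirement and chosen part-time work can be expected in both the cancer group and the population.

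Two errors of reporting could follow. A pooled result could be presented as the answer to hypothesis 3 when it answers a different question. And if chosen changers do better than unchosen ones, a real deficit after involuntary work loss could look smaller than it is. Because the hypothesis predicts a clinically lower score, a reduced estimate could be read as refuting it.

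**Working it through.** **Comparing the texts.**

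| Analysis or statement | Exposed group | Compared with | Condition on choice |
|---|---|---|---|
| Hypothesis 3 | Substantial reducers, leavers | Still employed at 12 months | Yes |
| HRQoL model by work change | All who reduce or leave between time 1 and time 2 | All who do not | No |
| HRQoL comparison at time 2 | Cancer group | Comparison group | No; not split by work change |
| Probit model | Work participation modelled jointly with health | – | None stated |
| Aim 4 | Change in employment participation | – | No |

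No stated analysis supplies the hypothesis 3 contrast. The pooled model matches the exposure in aim 4.

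**What pooling does.** The article gives no effect size, standard deviation or power for this contrast, so there is no figure to reproduce. What follows is illustration.

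Let v be the voluntary share among changers, and D_inv and D_vol the deficits relative to those with no change. Then

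pooled deficit = (1 − v) × D_inv + v × D_vol.

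Assume D_inv = 5 SF-36 points:

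| v | D_vol = 0 | D_vol = −2 (a gain) |
|---|---|---|
| 20% | 0.8 × 5 = 4.0 | 4.0 − 0.4 = 3.6 |
| 40% | 0.6 × 5 = 3.0 | 3.0 − 0.8 = 2.2 |
| 60% | 0.4 × 5 = 2.0 | 2.0 − 1.2 = 0.8 |

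The direction can reverse. In SD units, with D_inv = 0.5 and v = 40%, a voluntary deficit of 0.25 gives 0.30 + 0.10 = 0.40, a deficit of 0.5 gives 0.50 (no dilution), and a deficit of 0.75 gives 0.60 (inflation).

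**Does the smaller group cost more than it gains?** Inputs:

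- 125 cases retained at 12 months (Sample size).
- Share changing taken as the share not working in the earlier Australian cohort cited in the Background: (621 × 0.33 + 354 × 0.40) / 975 = 0.355. This gives about 44.4 changers and 80.6 others.
- D_inv = 0.5 SD, D_vol = 0, two-sided 5% level (all assumed).

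SE = √(1/n₁ + 1/n₂) in SD units, and power ≈ Φ(effect/SE − 1.96). Pooled SE = √(1/44.4 + 1/80.6) = 0.187.

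| v | Pooled effect | Power, pooled | n involuntary | SE, involuntary only | Power, involuntary only |
|---|---|---|---|---|---|
| 20% | 0.40 | 57% | 35.5 | 0.201 | 70% |
| 40% | 0.30 | 36% | 26.6 | 0.224 | 61% |
| 60% | 0.20 | 19% | 17.8 | 0.262 | 48% |

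The interval widens by about 8%, 20% and 40% (SE ratios 0.201/0.187, 0.224/0.187 and 0.262/0.187). Under these assumptions, separating the groups still has more power in every row. The 35.5% covers people not working a full year after diagnosis. It omits reducers, and the model's window from 6 to 12 months could contain fewer leavers, so the true number of changers could be higher or lower.

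**The case against.** The strongest reply is that the Analyses sentence is compressed. It also drops the word substantially and gives the verb reduce no object, so it may be shorthand for the hypothesis 3 group. It also serves aim 4, for which pooling is correct. Aim 4's claim on the pooled contrast stands, and the contrast should stay. The shorthand reading does not settle the matter, because the sentence states a grouping and no other analysis states the missing one.

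The choice condition may also qualify only leaving the work force. On that reading, pooling reducers is no mismatch, but chosen and unchosen leaving are still combined.

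A reader might infer three stronger points that the documents do not support:

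- *That choice cannot be measured for leavers.* The listed items on expected resignation or dismissal, retirement and stopping plans, and disability all bear on leavers. Plans recorded at time 1 can be set against an exit by time 2. The list is condensed and the questionnaire is not shown. The Background promises findings for "government about the reasons for work cessation, the mechanisms people use to remain working and existing workplace support structures", which is compatible with a reason-for-stopping question being asked.
- *That the Discussion calls for cases to be split by choice.* It faults earlier work for being unable to isolate retirement choice without a non-cancer control group. Its remedy is the comparison group.
- *That the contrast is certainly diluted.* Sicker patients may choose to stop, so the voluntary deficit could equal or exceed the involuntary one.

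**Conclusion.** The mismatch is clear from the text. Hypothesis 3 is conditional on lack of choice, the stated HRQoL analysis by work change is not, and nothing else fills the gap. Followed as written, the plan answers aim 4's general question and leaves hypothesis 3 untested. This is a conflict between two stated elements, so it does not depend on what an unseen analysis plan might add.

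The numerical effect is conditional. If chosen changers fare better than unchosen ones, as the hypothesis implies, the pooled contrast understates the hypothesised effect: an assumed 5 points becomes 4.0, 3.0 or 2.0 at voluntary shares of 20%, 40% or 60% with no voluntary deficit. The documents give neither the share nor either effect. Confidence is high for the mismatch, but the direction and size of any bias are not established.

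**What to change.** Reconcile the hypothesis with the analysis:

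1. State whether the choice condition applies to reducers as well as leavers.
2. Classify changers as involuntary or voluntary by a rule fixed in advance. Use the items already listed (preferred against usual hours, reasons for part-time work, expected resignation or dismissal, retirement and stopping plans, disability items) and any reason-for-stopping question in the questionnaire.
3. Make involuntary change versus still employed at 12 months the hypothesis 3 contrast, on 12-month HRQoL. Involuntary reducers are themselves still employed, so say that they are not in the reference group.
4. Report voluntary changers as a separate group.
5. Keep the pooled contrast and label it as the aim 4 analysis.

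The cost is a recoded exposure and a smaller involuntary group with a wider confidence interval. The proxies are imperfect: someone too ill to work may not prefer more hours, for example. A direct reason item, if the questionnaire has one, should therefore take precedence over them.

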## Discussion

Despite the considerable number of Australians of working ages being diagnosed with cancer each year, surprisingly little is known about the impact of cancer on the workforce. With an ageing population, the Australian Government has recently implemented policies to encourage people to remain working longer and has increased access to personal superannuation funds and social security benefits (e.g. pension bonus schemes). The challenges presented to 'baby boomers' (those born during 1946-1961) differ from those facing previous generations because, as they approach normal retirement age, they may face caring responsibilities for both elderly parents and young grandchildren [27]. Female baby boomers may be disadvantaged financially due to working in occupations that were traditionally low-paid and female-dominated (i.e., nursing, secretarial, retail, teaching) and before equal pay legislation (pre-1960s) and compulsory superannuation laws. They may also have taken longer periods off work to raise families, compared to subsequent generations, and so collectively may have little retirement savings and financial security [27]. Middle-aged men with cancer may be at the height of their careers, and their sense of self may be strongly attached to their work roles. Therefore, cancer may negatively affect a person's employment and financial situation and fuel the anxiety and distress created from facing a life-threatening illness.

Our research will extend the current literature and improve our understanding in this field. The translation of current knowledge into supportive care practice is limited because of the use of retrospective or cross-sectional designs and/or, patient groups from a single clinical setting, a dominance of breast cancer among the patient samples and, importantly, the inability to isolate the effects of ageing, retirement choice and labour force changes due to the lack of a non-cancer control group. Our study will overcome these limitations by recruiting a population-based sample and using validated instruments, including a non-cancer comparison group and utilising both a prospective and retrospective design. We have chosen colorectal cancer because this cancer type is the most common to both men and women, and we will have a homogenous disease group from which to compare men and women.

The study will address an important issue in cancer survivorship in greater detail than previously reported and, in doing so, will provide further insights into living with cancer and the potential implications for individuals, families and workplaces. It will also advance methods in economic evaluations of health care where a better understanding of productivity losses is gaining importance. Further, this project will identify specific issues and barriers faced by cancer survivors who want to remain employed, and provide practical information to supportive cancer care providers able to directly translate this information into developing resources for newly diagnosed cancer patients.
